## Abstract

**Background:**

Radiotherapy as a complement or an alternative to neurosurgery has a central role in the treatment of skull base grade I-II meningiomas. Radiotherapy techniques have improved considerably over the last two decades, becoming more effective and sparing more and more the healthy tissue surrounding the tumour. Currently, hypo-fractionated stereotactic radiotherapy (SRT) for small tumours and normo-fractionated intensity-modulated radiotherapy (IMRT) or proton-therapy (PT) for larger tumours are the most widely used techniques. It is expected a decrease of the risk of cognitive impairment with these modern techniques. However prospective data about cognitive long-term consequences of partial brain irradiation with SRT, PT, or IMRT remain very scarce to date.

**Methods:**

CANCER COG is one of the first multicentric study in the world to prospectively assess the cognitive performances of patients following different modalities of cerebral radiotherapy (stereotactic radiotherapy, proton therapy, intensity modulated radiotherapy) for the treatment of grade I-II skull base meningioma, up to at least 10 years after the end of radiotherapy. This longitudinal study includes the follow-up of 3 cohorts, including: patients treated with PRT, IMRT, and SRT. An additionally control group will be formed. The primary objective is to report long-term cognitive deterioration in each cohort until 10 years after the end of irradiation. The rate of clinical symptomatology improvement over time after irradiation, the evolution of health-related quality-of-life, anxiety/depression, fatigue, over time after irradiation, the tumoral local control after irradiation, the progression-free survival (PFS), the professional reintegration for working-age patients will also be assessed. CANCER COG aims to help clinicians to choose the best irradiation techniques with the best benefit/risk ratio. Inclusions started on september 2023.

**Trial registration:**

The study was registered on clinicaltrials.gov with the following number: NCT 06036706.

**Supplementary Information:**

The online version contains supplementary material available at 10.1186/s13014-025-02591-1.

## Background

Brain tumours represent a heterogeneous group of diseases with a variable prognosis depending on their histological type and topography. Low-grade brain tumours constitute a separate entity for which the goal of treatment is curative, and for which long patient survival is expected. Benign (grade I) and atypical (grade II) meningioma are the most frequent of them.

Radiotherapy as a complement or an alternative to neurosurgery has a central role in the treatment of these tumours. Radiotherapy techniques have improved considerably over the last two decades, becoming more effective and sparing more and more the healthy tissue surrounding the tumour. Currently, hypo-fractionated stereotactic radiotherapy for small tumours and normo-fractionated intensity-modulated radiotherapy for larger tumours or those close to high-risk structures are the most widely used techniques. To a smaller extent, because of its limited accessibility (< 100 centers worldwide), proton-therapy is a preferred technique for treating these low-grade brain tumours. Proton-therapy is a form of radiotherapy based on the use of accelerated protons, which stop at a given depth depending on their initial energy (Bragg peak). Proton-therapy thus avoids any exit dose. It is therefore dosimetrically superior to other conventional radiotherapy modalities using photons, whose substantial exit dose is only compensated by ballistic optimisation (multiple beams, fluence modulation, etc.). The sparing of healthy tissues at risk of complications is therefore maximal in the case of irradiation with a proton beam.

However, despite these technological improvements, radiotherapy may be a source of mid or long term radiation-induced complications, and having a strong impact on the patient’s personal and professional life. Among these side effect, memory and attention disorders are the complications the most feared by the radiation oncologist [1]. These cognitive problems, which can have a major effect on quality of life, can be mild to moderate, and may sometimes lead to dementia [2]. While the neurotoxicity associated with conventional brain radiotherapy (notably whole brain irradiation) is now relatively well documented [3–5], data about cognitive long-term consequences of partial brain irradiation with modern technical remain very scarce to date [6–8].

We recently showed, in a pilot study conducted among 16 patients (clinicaltrials.gov NCT02791360) who had been treated with radiotherapy for a good prognosis brain tumour at least 10 years previously, that radiotherapy appeared to accelerate brain ageing with an effect of dose, and time since completion of radiotherapy.

## Hypothesis and expected clinical outcomes

Following these observations, we herein propose the first study in France to prospectively assess the cognitive performances of patients following different modalities of cerebral radiotherapy (stereotactic radiotherapy, proton therapy, intensity modulated radiotherapy) for the treatment of low grade skull base meningioma, up to at least 10 years after the end of radiotherapy. This project is elaborated with the expertise of the National Cancer and Cognition Platform (http://www.canceretcognition.fr/), as well as of the National Clinical research Platform for Quality of Life in Oncology, both labelled by the French League against Cancer (LNC).

For the purpose of this research, we will constitute several cohorts of patients, treated either by intensity-modulated radiotherapy, stereotactic radiotherapy or proton-therapy. This will allow better understanding the cognitive and anatomical damages caused by new radiotherapy techniques and better understanding how ionising radiation (X-rays or protons) acts in the long term on brain tissue. Longitudinal follow-up will be multimodal, based on yearly multi-parametric brain MRI to assess morphological changes [9–11], in relation with dosimetric data as well as neuropsychological performances, health-related quality of life, anxiety and depression disorders, memory tasks, and socio-professional reintegration. This will notably make it possible to evaluate the relationship between dosimetric data, age at the time of treatment, region of the brain irradiated, type of radiation used, dose per fraction, neurocognitive and neuro-anatomical consequences. A Normal Tissue Control Probability (NTCP) model will be also developed. Overall, the results of this study should contribute to the improvement of treatment techniques, in particular by preserving as much as possible the significant cerebral zones (hippocampi, frontal lobe, sub-ventricular zones, etc.), and to the management of patients by proposing appropriate support measures. In the proton-therapy cohort, evaluations will make it possible to establish more precisely the place that this new irradiation strategy should occupy in the management of low grade meningioma. Importantly, we have planned to constitute a last cohort, with subjects free of any neurological disease, to make it easier the interpretation of cognitive performances over time among patients in the three brain radiation cohorts.

## Methods

CANCER COG is a multicenter prospective longitudinal study with the constitution and the follow-up of 4 cohorts, including:

Three cohorts of patients candidate for a brain irradiation following the diagnosis of benign meningioma or atypical meningioma:
Cohort “IMRT”: Patients receiving normo-fractionated intensity-modulated brain irradiation with or without stereotactic positioning (IMRT, VMAT, Tomotherapy…).Cohort “SRT”: Patients receiving hypo-fractionated stereotactic brain irradiation.Cohort “PRT”: Patients receiving normo-fractionated proton therapy brain irradiation.
In addition, a control group with participants free of brain disease will be constituted:
Control cohort: Participants without any meningioma or neurological comorbidities.

### Primary objectives and endpoints

The primary objective is to report long-term cognitive deterioration among patients with a diagnosis of skull base benign meningioma, or atypical meningioma treated by fractionated proton-therapy (PRT) or hypo-fractionated stereotactic radiotherapy (SRT) or normo-fractionated intensity-modulated radiotherapy (IMRT), 10 years after the end of irradiation.

The primary endpoint is the proportion of patients with an impairment in cognitive parameters 10 years after irradiation of skull base benign meningioma, or atypical meningioma.

Cognitive impairment is defined as a clinically significant deterioration, in comparison with baseline evaluation (before brain irradiation), in neurocognitive test scores, grouped into five cognitive domains:

Attention/information processing speed,executive functioning,episodic memory,working memory,short term memory.

Deterioration is either defined as (i) the occurrence of cognitive impairment (a total of ≥ 5 impaired z-scores, as considered in Douw et al. 2009) among patients who were not cognitively impaired at baseline, or (ii) the worsening of cognitive impairment (≥ 2 supplementary impaired z-scores) among patients who were already cognitively impaired at baseline.

Scores will be converted to z-scores by subtracting mean and dividing by standard deviation (SD) of data of participants free of brain disease from the control group. A z-score of at least 2 SD below normative data is defined as impaired.

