**With regard to brain MRI parameters**:
To evaluate, according to 3 modalities of brain irradiation (PRT, SRT, IMRT), alterations/modifications of grey and white matters over time after irradiation on brain MRI and their correlation with cognitive deterioration.To correlate cognitive deterioration with MRI changes.To constitute a biological collection to further explore potential biomarkers predictive of radio-induced toxicities.

For participants free of brain disease:

To report cognitive performances (cognitive functions and complaints) over time using the same timetable as for patients.

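### The primary endpoint's z-scores use a crude control mean and SD with no stated reference visit and no age term, so deterioration depends partly on age and possibly on ordinary ageing or practice

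*Protocol article*

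**What the plan says.** Primary objectives and endpoints (Protocol article) gives the conversion in full: scores are "converted to z-scores by subtracting mean and dividing by standard deviation (SD) of data of participants free of brain disease", meaning the control group. The cut-off follows: "A z-score of at least 2 SD below normative data is defined as impaired". A patient not impaired at baseline deteriorates through "the occurrence of cognitive impairment (a total of ≥ 5 impaired z-scores"); for the others the criterion is "the worsening of cognitive impairment (≥ 2 supplementary impaired z-scores) among patients who were already cognitively impaired at baseline".

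The control cohort is described in Methods only as "Participants without any meningioma or neurological comorbidities". Its members are followed "using the same timetable as for patients", and Table 2 gives them the same cognitive visits (baseline, 6 and 12 months, then 3, 5, 7 and 10 years). Hypothesis and expected clinical outcomes gives their purpose: "to make it easier the interpretation of cognitive performances over time among patients".

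Eligibility criteria admits patients over 20 and under 65 years. Statistical design overview plans 31 assessable controls. The primary analysis is a proportion with a 95% confidence interval in each cohort.

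**The concern.** The conversion is written into the endpoint definition, so an analysis plan that follows it literally inherits it. Two things are left unfixed.

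- **Reference visit.** If the controls' baseline data serve as the norm at every visit, ten years of ordinary decline moves patients towards the cut-off. Gains from being tested seven times move them away from it. Neither has to do with irradiation.
- **Age.** One mean and SD per test is applied across a 45-year span of entry ages. An older patient starts nearer to the cut-off and crosses it more easily. Because the rule counts scores below a fixed threshold, comparison with the patient's own baseline does not cancel this.

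No later step corrects either point, since the primary analysis reports only a proportion per cohort. Deterioration status also feeds the dosimetric and MRI tests and the planned NTCP model. Hypothesis and expected clinical outcomes wants to relate outcome to age at treatment, which is awkward if the outcome depends on age by construction.

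**Working it through.** **The plan's own figure.** At p = 0.5 the full width of the Wilson 95% interval is 1.96/√(n + 1.96²). For n = 93 this is 1.96/√96.84 = 0.199; for n = 92 it is 0.2002. The stated 93 is reproduced, and this point does not change it. For a cohort of 31 the width is 1.96/√34.84 = 0.332, or about ±17 percentage points.

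**Inputs from the protocol.** 31 controls; impaired score at z ≤ −2; deterioration at 5 or more impaired scores, or 2 or more additional ones if already impaired; 10 years.

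**Assumed inputs, not in the protocol.** 20 scores, inter-test correlation 0.3, retest correlation 0.7, ageing 0.02 to 0.03 SD a year, entry ages uniform on 35 to 65, no radiation effect, no practice effect.

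**One score, by hand.** Take 0.03 SD a year and controls of the same age mix (mean 50). Age spread has variance 30²/12 = 75, so the raw control SD is √(1 + 0.03² × 75) = 1.033 and the cut-off lies at −2 × 1.033 = −2.066. Probability of an impaired score at 10 years:

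| Entry age | Same-visit reference | Baseline reference |
|---|---|---|
| 40 | Φ(−2.066 − 0.3) = 0.9% | Φ(−2.066) = 1.9% |
| 60 | Φ(−2.066 + 0.3) = 3.9% | Φ(−2.066 + 0.6) = 7.1% |

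**Full rule, by simulation.** 300 control samples of 31, each with 4,000 patients. Entries are the percentage classed as deteriorated: all patients (over 55 / under 45).

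| Controls | SD/year | Baseline reference | Same-visit reference | Same visit, age-regressed |
|---|---|---|---|---|
| Same age | 0.02 | 3.2 (5.4 / 1.4) | 1.5 (2.6 / 0.6) | 1.6 (1.6 / 1.8) |
| Same age | 0.03 | 4.8 (9.1 / 1.3) | 1.6 (3.2 / 0.3) | 1.6 (1.7 / 1.6) |
| 10 years younger | 0.02 | 5.9 (9.3 / 2.9) | 2.9 (4.7 / 1.3) | 1.9 (2.6 / 1.4) |
| 10 years younger | 0.03 | 10.2 (17.8 / 3.8) | 3.9 (7.3 / 1.2) | 1.9 (2.4 / 1.5) |

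Other runs with these inputs agree: 3% to 5% and about 1.6% for controls of the same age, 5% to 11% and 3% to 4% for younger controls.

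**Masking and offset.** These runs vary the scores from 15 to 25 and the inter-test correlation from 0.3 to 0.5. A net practice gain of 0.3 SD gives 0.2% to 1.1% with a baseline reference against 1% to 4% with a same-visit reference. A patient–control offset of −0.5 to −1.0 SD with no shift over time gives 4% to 21% under either reference. A same-visit reference therefore removes the common shift over time; only adjustment or matching removes the offset.

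**The case against.** A reader might infer that the controls are unmatched and that their baseline data are the norm, so that ageing is certainly counted as deterioration. The document supports neither. It is a condensed article, its control description is one line, and matching may be set out in the full protocol. Controls are retested at the patients' visits in order to help read performance over time, so a same-visit reference is at least as natural a reading. It brings the rate with same-age controls down to about 1.6%.

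The size also deserves restraint. Every percentage rests on assumed test counts, correlations and slopes, and the larger ones need younger controls or a baseline reference. With same-age controls the artefact is small beside the planned precision of about ±10 points overall and ±17 per cohort. Even in the least favourable row, more than 80% of patients over 55 are not classed as deteriorated. For the secondary patient-level analyses the plan disclaims comparison between arms.

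What remains is that the conversion is a stated rule, and it carries neither a visit nor an age term. With same-age, same-visit controls the overall proportion is hardly affected, but who is classed as deteriorated still depends on age. A cohort older than the controls would have its own proportion shifted. Modality is chosen by the radiation oncologist and SRT is not allowed for grade II, so cohort ages may differ. Both the Abstract and the Discussion expect the results to guide the choice of technique.

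**Conclusion.** The point holds as a defect in how the endpoint is specified: the conversion names no reference visit and makes no allowance for age. It does not hold as a claim that the controls are unmatched or that normal ageing will in fact be counted; that depends on choices the text leaves open.

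Under the assumed inputs and no radiation effect, the reference visit alone moves the rate from about 1.6% to 3% to 5% with same-age controls, and from 3% to 4% up to 5% to 11% with controls 10 years younger. Under a same-visit reference with same-age controls, the rate is still about 3% over 55 against about 0.5% under 45; age-regressed norms bring both to about 1.7%. The direction of the age effect needs only that scores fall with age; its size depends on the assumptions. The change should be made, but the sample size is not affected.

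**What to change.** In Primary objectives and endpoints, replace the conversion by: at each visit, z = (patient's score − score expected for that patient's age, and education if recorded, from a regression in the controls at the same visit) / between-subject SD of the controls around that expected score. State the age range and any matching of the controls, and keep the raw z-score as a sensitivity analysis.

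The denominator must be the total residual SD, not the within-person residual SD of a mixed model fitted to all visits. At a retest correlation of 0.7 the latter is √(1 − 0.7) = 0.55 of the total. The −2 cut-off would then fall at −2 × 0.55 = −1.1 population SD, and Φ(−1.1) ≈ 14% of healthy scores would be flagged instead of 2.3%.

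The cost is wording, modest analysis work, a few degrees of freedom from 31 controls and slightly noisier norms. If controls are much younger than patients, the regression extrapolates and some gradient stays (2.4% to 2.6% over 55 against 1.4% to 1.5% under 45 in the table), which is a reason to watch the controls' ages during recruitment. The control assessments are already scheduled; whether education is recorded is not stated. Inclusion began in 2023, so no ten-year assessment can exist before 2033 and the rule can be fixed well before those data.

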### Secondary objectives and endpoints

The secondary objectives are:

at the patient level
To report cognitive performances over time after brain radiotherapy for the treatment of skull base grade I-II meningioma, after the end of irradiation, according to 3 modalities of radiotherapy (PRT, SRT, IMRT).To evaluate, among patients according to 3 modalities of brain radiotherapy: the delay from radiotherapy start to cognitive deterioration, the rate of clinical symptomatology improvement over time after irradiation, the evolution of health-related quality-of-life, anxiety/depression, fatigue, over time after irradiation, the tumoral local control after irradiation according to rano guidelines [12] and the progression-free survival (PFS), the professional reintegration for working-age patients, the changes of cognitive functions and cognitive complaints over time after radiotherapy.
**With regard to radiotherapy parameters**:
To evaluate, according to 3 modalities of brain irradiation (PRT, SRT, IMRT), the correlation between dosimetric data and cognitive deterioration onset.To build tumoral control probability (TCP) and normal tissue complication probability (NTCP) on the basis of the prospective evaluations of patients.
**With regard to brain MRI parameters**:
To evaluate, according to 3 modalities of brain irradiation (PRT, SRT, IMRT), alterations/modifications of grey and white matters over time after irradiation on brain MRI and their correlation with cognitive deterioration.To correlate cognitive deterioration with MRI changes.To constitute a biological collection to further explore potential biomarkers predictive of radio-induced toxicities.

For participants free of brain disease:

To report cognitive performances (cognitive functions and complaints) over time using the same timetable as for patients.

### Trial schedule

CANCER COG is a multicenter prospective longitudinal study with the constitution and the follow-up of 4 cohorts:

Cohort “IMRT”: Patients receiving normo-fractionated intensity-modulated brain irradiation with or without stereotactic positioning (IMRT, VMAT, Tomotherapy…).Cohort “SRT”: Patients receiving hypo-fractionated stereotactic brain irradiation.Cohort “PRT”: Patients receiving normo-fractionated proton therapy brain irradiation.Control cohort: Participants without any meningioma or neurological comorbidities.

The overall duration of the project is estimated to 15 years, including 5 years of inclusion and around 10 years of participation.

### Statistical design overview

The primary endpoint is the proportion of patients with an impairment in cognitive parameters 10 years after irradiation of skull base benign meningioma, or atypical meningioma.

As there are no available data in the literature concerning the prevalence of long-term cognitive disorders after radiotherapy treatment of skull base benign meningioma, or atypical meningioma, we assume that approximately 50% of patients will present an impairment of their cognitive functions 10 years after the end of irradiation. Using a 95% confidence interval with a width of 0.2 for a small sample size, a total of 93 patients is required.

In order to document the impact of brain irradiation on cognitive performances for each of the 3 radiotherapy modalities usually used in this indication, 31 patients are required in each of the 3 cohorts (IMRT, SRT, PRT).

In addition, a control group with 31 assessable participants free of brain disease will be constituted.

In order to anticipate 15% of subjects possibly non assessable, 36 subjects per each of the 4 cohorts will be enrolled, for a total of 108 patients and 36 participants free of brain disease.

Categorical variables will be summarized using numbers and proportions. Quantitative variables will be summarized using quartiles and range (mean and standard deviation for Gaussian-like variables). The pattern of missing data will be described.

Briefly, all outcomes will be analyzed based on intention-to-treat principle. For each cohort, the Intention to Treat (ITT) population is defined as all patients included in this radiation arm, regardless of whether eligibility criteria are met and whether or not radiation therapy is used.

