#### Primary objective

The proportion of patients with an impairment in cognitive parameters 10 years after irradiation of skull base grade I-II meningioma will be estimated with a 95% confidence interval in each cohort.

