#### Secondary objectives

At the patient level: no comparison between arm is planned in analyses.

The Progression-Free Survival (PFS) time is defined as the time elapsed from treatment start to progression disease or death from any cause. Data of patients who did not experience event are censored at the last assessment date. PFS will be estimated by the Kaplan-Meier method. The evolution of health-related quality-of–life after irradiation will be described by mean and standard error, and compared across time by the Student t test for paired data.

With regard to radiotherapy parameters: in each cohort, the correlation between dosimetric data (quantitative data) and the occurrence of cognitive deterioration will be assessed by the non-parametric Wilcoxon Mann Whitney test.

With regard to brain MRI parameters: In each cohort, association between alterations or modifications of grey and white matters after irradiation on brain MRI and cognitive deterioration will be assessed by the exact Fisher test.

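### The 95% CI width of 0.2 holds only for 93 patients pooled; the primary estimates are per cohort with 31 patients, where the width is about 0.33 to 0.37

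*Protocol article*

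**What the plan says.** The sample size is set out in the Protocol article, Statistical design overview. It starts from an assumed proportion, "we assume that approximately 50% of patients will present an impairment of their cognitive functions 10 years after the end of irradiation", and continues: "Using a 95% confidence interval with a width of 0.2 for a small sample size, a total of 93 patients is required". The next paragraph divides this total between the modalities: "31 patients are required in each of the 3 cohorts (IMRT, SRT, PRT"). No precision is given for 31. Enrolment then follows: "In order to anticipate 15% of subjects possibly non assessable, 36 subjects per each of the 4 cohorts will be enrolled", which makes 108 patients plus 36 control participants.

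The section Primary objective (under the statistical design) says that the proportion impaired at 10 years "will be estimated with a 95% confidence interval in each cohort". The Methods paragraph of the abstract agrees: "The primary objective is to report long-term cognitive deterioration in each cohort until 10 years after the end of irradiation". Neither place mentions an estimate over the three irradiated cohorts together. Under Secondary objectives the article adds that, at the patient level, "no comparison between arm is planned in analyses".

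**The concern.** The design tests no hypothesis for its primary endpoint, so the width of the confidence interval is the whole justification of the sample size. That width is computed for the 93 patients taken together, and 31 is simply 93/3. The analysis then uses the three groups of 31 separately. If so, the only stated precision belongs to an estimate that is not planned, and the estimates that are planned have no stated precision.

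The Discussion says the results should help radiation oncologists choose a technique, so readers will use the per-modality proportions. Someone who carries the stated width over to them would expect roughly plus or minus 10 percentage points.

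The allowance for non-assessable subjects also looked slightly short.

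**Working it through.** **Inputs**, all from Statistical design overview: p = 0.5; two-sided 95% interval (z = 1.96, z² = 3.84); full width 0.2; total 93; 31 per cohort; 15% non-assessable; 36 enrolled per cohort. The unit of analysis, each cohort, comes from Primary objective and the abstract.

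**1. Reproduce 93.** At p = 0.5 the full widths simplify to:

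- Wilson (and Agresti-Coull, identical at p = 0.5): z/√(n + z²)
- Wald: z/√n

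Setting the Wilson width to 0.2 gives n = (1.96/0.2)² − 3.84 = 96.04 − 3.84 = 92.2, so 93. Check: n = 92 gives 0.2002 and n = 93 gives 0.1992. Other methods do not give 93: Jeffreys 94, Wald 97, Clopper-Pearson 104. The stated figure is therefore right as a total under a Wilson-type interval.

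**2. Same target, 31 patients.**

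| Method | Width at n = 31, p ≈ 0.5 | Ratio to 0.2 |
|---|---|---|
| Wilson | 1.96/√34.84 = 0.332 | 1.66 |
| Wald | 1.96/√31 = 0.352 | 1.76 |
| Clopper-Pearson (15/31: 0.302 to 0.669) | 0.368 | 1.84 |

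The Wilson interval at 50% is 0.5 ± 0.166, or 0.33 to 0.67. With 93 it would be 0.40 to 0.60.

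**3. Can another reading rescue 0.2 per cohort?**

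- *All 36 enrolled assessable:* Wilson 0.311, Clopper-Pearson 0.342. No.
- *A different true proportion:* the Wilson width at n = 31 is 0.308 at p = 0.3, 0.274 at p = 0.2 and 0.218 at p = 0.1. No.
- *0.2 as a half-width (full width 0.4):* n = (1.96/0.4)² − 3.84 = 24.01 − 3.84 = 20.2, so 21. That does not give 93.

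**4. What 0.2 per cohort would take.** By the method that gives 93, it takes 93 assessable per cohort, or 3 × 93 = 279. With 15% loss, 93/0.85 = 109.4, so 110 enrolled per cohort.

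**5. Loss allowance.**

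- 36 × 0.85 = 30.6, below 31; 108 × 0.85 = 91.8, below 93.
- 31/0.85 = 36.5, so 37 would be needed.
- 36 tolerates a loss of 1 − 31/36 = 13.9%.
- If each subject is lost independently with probability 0.15, the chance that 36 enrolled leave at least 31 assessable is 54% per cohort.

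**The case against.** The strongest defence is that the sizing was meant to be pooled. The sample-size sentence speaks of a total, the section Primary objectives and endpoints words the endpoint as one proportion without naming a cohort, and the text never promises a precision for 31. All of this is accurate, and 93 is not a calculation error. It does not settle the matter, because the analysis section and the abstract both fix the estimate per cohort. If a pooled estimate was intended, it is the analysis section that leaves out the estimate for which the study was sized. The two sections disagree on either reading.

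A second defence is that little depends on the figure: the study is descriptive, each interval will be reported at its actual width, and nothing will be biased. That is true of the final estimates. But the width is the only rationale for the sample size of the primary endpoint, and it describes something other than what will be estimated.

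On the loss allowance, 31 × 1.15 = 35.65 rounds up to 36, so the authors evidently added 15% where dividing by 0.85 was needed. The gap is one patient per cohort and immaterial for precision: with 30 patients the Wilson width is 0.337 against 0.332 with 31. The 54% figure also treats 31 as a threshold, which the article does not do. This part is a minor correction, and the main point does not depend on it.

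**Conclusion.** The concern holds. As written, the design precision of 0.2 applies to no planned primary estimate. At the assumed 50%, each cohort's interval will be about 0.33 to 0.37 wide, roughly plus or minus 17 to 18 percentage points where 10 is implied. This assumes 31 assessable patients per cohort and one of the three usual intervals; a continuity-corrected Wald interval would be slightly wider, at 0.384. A proportion away from 50% narrows the interval, but even at 10% it stays above 0.2. The shortfall in the loss allowance is real and small.

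**What to change.** Keep the enrolment and correct the statement in Statistical design overview, for example:

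> With 31 assessable patients in a cohort, the 95% Wilson confidence interval for a proportion of 50% is about 0.33 wide. The width of 0.2 refers to the 93 irradiated patients taken together.

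The interval method belongs in that sentence, because both 93 and 0.33 depend on it.

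If 0.2 is to remain the design precision, add the pooled proportion over the three irradiated cohorts to the Primary objective analysis as the estimate to which it refers. It would describe an equal mix of the three modalities, since the cohorts are the same size by design. If only per-cohort estimates are wanted, give the per-cohort width as the design precision and drop 0.2.

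Restate the allowance for non-assessable subjects as about 14% (36 enrolled for 31 assessable).

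The cost is wording and a less favourable stated precision. No patients, visits or analyses are added, apart from the one pooled proportion if that option is taken.
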